### Follow-up

All the patients will be under follow-up for a time period of 3 weeks after the completion of treatment by means of telephonic interviews or face-to-face evaluations. The schedule pertaining to the BXD and waitlist groups is shown in Tables 1 and 2, respectively. The reasons for patient dropouts or withdrawals will be recorded in the case report form.

### Outcomes

#### Primary outcome

In the present study, the primary outcome will be the variation in the scores pertaining to the global scale of the Quality of Life Questionnaire for Functional Digestive Disorders (FDDQL) after 3 weeks. FDDQL is a questionnaire with forty-three items and eight subdomains (activities, anxiety, diet, sleep, discomfort, health perceptions, coping with disease, and impact of stress), used for the evaluation of the quality of life in patients with functional digestive disorders [18]. A validated Chinese version of the FDDQL will be adopted for the study (Cantonese in Hong Kong) [19, 20].

#### Secondary outcomes

The timeline with reference to the evaluation of the secondary outcomes is shown in Tables 1 and 2.

##### Hospital Anxiety and Depression Scale

The Hospital Anxiety and Depression Scale (HADS) is a 14-item, self-administered scale used to assess the psychological distress in non-psychiatric patients [21]. As suggested by the consensus on FD, HADS is the recommended scale for the assessment of the psychological impact of *Wei-Pi* syndrome [9]. The present study will employ a validated Chinese-Cantonese version of the HADS [22].

##### EuroQoL 5-dimension 5-level

EuroQoL 5-dimension 5-level (EQ-5D-5L) is a five-item instrument used for the assessment of the generic health status, including mobility, self-care, usual activities, pain/discomfort, and anxiety/depression. The questionnaire was developed by the EuroQol Group in 2009 and is available in 130 languages (https://euroqol.org/). The EQ-5D-5L has been effectively used to measure the quality of life in patients with dyspepsia [23, 24].

##### Liver and kidney function tests

The patients will undergo liver and kidney function tests before and after the completion of therapy using modified BXD, in order to ensure patient safety and to determine the adverse effects of modified BXD. The blood AST, ALT, and creatinine levels of the patients will be evaluated using an automated chemistry analyzer (Sysmex BX-3000, Japan) in the Chung Tai X-Ray & Medical Laboratory Limited, Hong Kong.

##### Adverse events

Subjects will be asked to report any adverse events according to the monitoring form in the patient diary. The self-rated intensity of adverse events (mild, moderate, severe) and perceived causal relationship to intervention (unrelated, unlikely, possibly related, probably related, definitely related) will be recorded [25].

##### Medications

Medications that are prescribed by the doctors to relieve postprandial distress syndrome will not be restricted. The usage (dosage, frequency, and duration) of the medications will be recorded and analyzed.

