A unique feature of CM is the treatment based on syndrome differentiation, wherein the patient receives an individualized herbal prescription, in line with the body constitution of the patient and the pathological factors associated with the symptoms [10, 11]. The common pathological factors that contribute to the *Wei-Pi* syndrome include exterior pathogen invasion, food stagnation, phlegm stagnation, mental dissatisfaction, and spleen-stomach vacuity [12]. *Wei-Pi* syndrome is differentiated into five patterns in Chinese medicine (CM): (1) spleen deficiency and qi stagnation, (2) liver qi invading the stomach, (3) spleen-stomach dampness-heat, (4) spleen-stomach deficiency cold, and (5) cold-heat complex pattern [8, 9]. Banxia Xiexin decoction (BXD), first documented in the CM classic, the *Treatise on Cold Damage and Miscellaneous Diseases*, is a classic formulation for the treatment of *Wei-Pi* syndrome with the cold-heat complex pattern [8, 9]. BXD is used to direct the qi downwards, in order to relieve the hiccup, dissipate the fullness and satiation, and harmonize the cold-heat in the patient’s stomach. As the clinical manifestation of symptoms may vary from patient to patient, general clinical practice adopts an approach that involves the addition of specific herbs to the BXD, in accordance with the respective syndrome differentiation (termed modified BXD). Recent clinical studies have reported that BXD is effective in the treatment of *Wei-Pi* syndrome and improves the symptoms of FD by regaining the gastric emptying rate, reducing the mucosal damage, improving the gastrointestinal function, and inducing anti-inflammatory action against *Helicobacter (H.) pylori* [13–15]. However, evidence regarding the effect of BXD on FD remains inconclusive, on account of the methodological flaws in the aforementioned studies.

The present study aims to evaluate the efficacy of modified BXD in the management of *Wei-Pi* syndrome through a randomized, waitlist-controlled trial. A semi-standardized treatment protocol based on syndrome differentiation will be adopted, in order to fulfill the CM theory on diagnosis and treatment, and to ensure scientific rigor of the trial design. A waitlist control group will be used, owing to the unavailability of an inert placebo for BXD.

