### Blinding

This is an open-label study. The patients and Chinese medicine practitioners (CMPs) will be informed regarding the allocation of patients into the two groups. CMPs will perform syndrome differentiation and prescribe the modified BXD, in accordance with the patient’s pattern of differentiation. The investigators who assess the outcomes will be blinded to the allocation and will not be involved in the diagnosis and treatment. Moreover, the coded information pertaining to the patients will be used for data entry and data analysis, and the group allocations will be masked during this process.

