#### Control group

The patients in the waitlist control group will be under observation during the 3-week waiting period. Subsequently, they will undergo the same treatment and follow-up as the BXD group, in order to minimize the nocebo effect.

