#### Concomitant treatment

Medications and standard care for postprandial distress syndrome will not be restricted. A patient diary will be used to document the use of medications and adverse events in the patients.

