#### Statistical analysis

The data collection and entry into the computer will be performed by the assessors using the method of double data entry. The collected data will be sent to the statistician without identifiers. The data will be analyzed using the SPSS 24.0. The principle of intention-to-treat analysis will be used with multiple imputations. Continuous data will be analyzed by means of the *t* test or Wilcoxon rank-sum test; categorical data will be analyzed using Fisher’s exact test or Wilcoxon rank-sum test.

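### With unrestricted PDS medication in an open-label trial, the week-3 FDDQL comparison estimates BXD added to usual care; the planned analyses cannot show how far drug changes affect it

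*Protocol article*

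**What the plan says.** The Concomitant treatment section sets the same policy for both groups: "Medications and standard care for postprandial distress syndrome will not be restricted". The Medications section, under Secondary outcomes, repeats this for prescribed drugs ("Medications that are prescribed by the doctors to relieve postprandial distress syndrome will not be restricted") and adds: "The usage (dosage, frequency, and duration) of the medications will be recorded and analyzed". Tables 1 and 2 list concomitant medications at every contact, including days 0, 7, 14 and 21 in both groups.

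The Blinding section states: "This is an open-label study". Patients and practitioners know the allocation; outcome assessors do not.

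The Control group section describes the comparator as follows: "The patients in the waitlist control group will be under observation during the 3-week waiting period". The Background gives the aim: "The present study aims to evaluate the efficacy of modified BXD in the management of" Wei-Pi syndrome, by a randomised comparison with a waitlist.

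The primary outcome is the change in the "global scale of the Quality of Life Questionnaire for Functional Digestive Disorders (FDDQL) after 3 weeks". Under Statistical analysis, the principle is intention to treat with multiple imputation. The test is introduced with "Continuous data will be analyzed by means of the", followed by the t test or the Wilcoxon rank-sum test. No medication term is mentioned.

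**The concern.** A waitlist patient who knows that treatment is three weeks away and still has symptoms may start or increase a PDS drug. A patient on BXD may cut one down, or start one. Any of these can happen before day 21 and can act on the FDDQL, which is a questionnaire on quality of life.

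What is at stake is the reading of the result. A small week-3 difference could mean that BXD adds little, or that it did work which drugs did in the control group. A large difference could partly reflect drugs started in the BXD group. A conclusion worded as the efficacy of BXD against observation would not distinguish these. A conclusion worded as an add-on effect would be correct in every case, but would still leave the contribution of drug changes unknown.

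**Working it through.** **Which contrast the design delivers.** Both groups may use PDS drugs and standard care freely. One group also receives BXD from day 0; the other receives it after day 21. At day 21 the randomised contrast is therefore usual care plus BXD versus usual care with BXD still to come. Drug changes after allocation are part of that contrast.

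**What the medication analysis can show.** Drug records in both groups at days 0, 7, 14 and 21 can show whether use diverged before the primary assessment. If it did not, there is little left to explain. If it did, a comparison of usage alone does not give the FDDQL difference that would have been seen without the divergence, and the two-group test has no term for it.

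**Size.** The article gives no rate of drug use and no drug effect, so both are assumptions here.

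Inputs from Sample size: planning effect 0.6 SD; 42 per group; alpha 0.05, taken as two-sided because the article does not say. The article's own 22 per group before dropout is not reproduced by a two-sample calculation at 0.6 SD and 80% power, which gives 44 (45 by the t test). That is a separate matter; only the 0.6 and the 42 are used below.

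Assumed: the groups differ by q = 0.20 in the proportion with new or increased PDS drug use, and such use is worth e = 0.3 to 0.5 SD on the FDDQL, with the SD unchanged.

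- Shift in the difference = q × e: 0.20 × 0.3 = 0.06 SD; 0.20 × 0.5 = 0.10 SD.
- As a share of the planning effect: 0.06/0.6 = 10%; 0.10/0.6 = 17%.
- If use is higher on the waitlist, the observed difference becomes 0.60 − 0.06 = 0.54 or 0.60 − 0.10 = 0.50.

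Power of the two-sided t test uses the noncentral t distribution with 82 degrees of freedom and noncentrality d × √(42/2):

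| Difference (SD) | Noncentrality | Power, 42 per group |
|---|---|---|
| 0.60 | 2.75 | 78% |
| 0.54 | 2.47 | 69% |
| 0.50 | 2.29 | 62% |

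If use is higher in the BXD group, the same assumptions push the difference up to 0.66 to 0.70 SD.

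With the article's 15% dropout, 42 × 0.85 = 35.7 per group, and the three power figures become 71%, 61% and 55%.

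**The case against.** The strongest reply is that nothing is hidden and nothing is invalid. The drug policy is stated twice and is the same in both groups. Being under observation describes what the trial does with waitlist patients; it does not say that they go untreated. The aim is tied to a waitlist comparison, so an attentive reader can work out the add-on contrast. Intention to treat with free background care is a legitimate pragmatic choice. All of this stands. It makes the wording of the conclusion a matter of clarity, not the correction of an error.

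The method of the medication analysis may also sit in a full protocol or analysis plan that is not shown, so its absence from the article is no fault. That stands too.

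Several stronger readings are tempting and should not be drawn:

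- **That the week-3 comparison is biased.** It would be so only as an answer to a different question, namely the effect had nobody started or increased a drug. The article does not pose that question.
- **That drug use will differ between groups.** The design permits it; no figure in the article shows it, and the direction is open.
- **That only doctor-prescribed drugs are analysed.** The Medications text names these, but Tables 1 and 2 list concomitant medications under secondary outcomes with no limit by prescriber, and the diary has none either.
- **That total days of use will be distorted by longer follow-up on the waitlist (63 against 42 days).** No section proposes totalling use over the whole follow-up, and contacts match through day 21.

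What the reply does not remove is that the stated two-group test cannot say how much of the week-3 difference reflects drug changes, although the records needed to examine this are already scheduled.

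**Conclusion.** The concern holds in a limited form. The primary comparison is a valid randomised estimate of modified BXD added to usual care versus usual care with delayed BXD. It does not estimate BXD against mere observation, and the conclusion should not be worded as if it did. The planned medication analysis can reveal divergence in drug use, but not its effect on the FDDQL difference.

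The size is unknown. The 0.06 to 0.10 SD shift, and the fall in power from 78% to between 62% and 69%, rest entirely on the assumed 20-point difference and 0.3 to 0.5 SD drug effect, with more use on the waitlist. They illustrate scale and are not a forecast. A reader might infer that a null result would be uninterpretable. It would not: it would mean no detected add-on benefit, and the day 0 to 21 drug records would help in reading it.

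**What to change.** 1. Keep the intention-to-treat comparison as primary, and state its conclusion as the effect of modified BXD added to usual care versus usual care with delayed BXD.
2. Replace the unadjusted t test by a linear model for the change in FDDQL with group and PDS drug use at day 0 (yes/no). This handles chance imbalance and may add precision; it does not deal with changes after allocation.
3. Prespecify one supplementary analysis in which day-21 FDDQL after a started or increased PDS drug is set to missing and imputed with the multiple imputation already planned. Read it beside a between-group comparison of drug changes over days 0 to 21 (start, increase, decrease, stop). Decreases and stops appear only in that comparison, not in the imputation.

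The cost is small, because the drug records are already scheduled at every contact. The downside is a narrower conclusion and one more result that rests on an untestable imputation assumption. That assumption carries real weight here, since the FDDQL is not measured between day 0 and day 21. The definitions should be fixed before outcome data by group are seen. No restriction on medication is proposed.

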### Oversight and monitoring

A trial monitoring committee (TMC) comprising experts from the Chinese Medicine Department and the Chief Pharmacist’s Office in the Hospital Authority will oversee the trial, review the safety data, and provide advice regarding protocol modification or termination of the trial. The investigators will report the progress of the trial to the TMC on a quarterly basis, including the details regarding recruitments, adverse events, issues arising from the trial, and the difficulties encountered in relation to the study.

In view of the fact that the adverse events and interim analysis will be directly reported to the TMC, the trial will not involve a data monitoring committee. Serious adverse events will be immediately reported to the TMC and the HKU/HA HKW IRB.

The HKU/HA HKW IRB will review the study protocol and protocol amendments. The investigators will regularly submit an annual report to the IRB. The project management group, consisting of the principal and lead investigators, the Chief-of-Service, and the clinical manager of the HKBA-HKU CMCTR, will convene every month, in order to review the conduct of the trial.

### Safety and risk management

Insurance will be obtained to cover any potential damage during the study. The measures that will be taken to ensure patient safety are stated as follows.

#### Quality control of herbs

All the herbs used in the study will have to meet the import standards under the Regulation of Chinese Medicine in Hong Kong (The Chinese Medicine Ordinance, Cap. 549 of the Laws of Hong Kong). The herbs will be provided by qualified CM wholesalers approved by the Hospital Authority in Hong Kong. The heavy metal levels (arsenic, mercury, and lead) in the herbs will be evaluated, in order to ensure safety [26].

#### Liver and kidney function tests

All the patients will undergo liver and kidney function tests twice (prior to and after the administration of modified BXD).

In the event of the incidental detection of abnormal liver and/or kidney functions after the consumption of Chinese medicine, the patient will be referred to a doctor for further examination, monitoring, and/or treatment.

### Ethics

The study protocol is compliant with the ICH-GCP guidelines. The collection and storage of personal data and information will follow Chapter 486 of the Personal Data (Privacy) Ordinance. All data and personal information will be stored in a locked cabinet or a password-protected computer. Documents regarding the study will be retained for 3 years after the completion of the study. Subsequently, all the documents will be destroyed.

### Statistical methods

#### Sample size

In our pilot observations, the global score of FDDQL pertaining to the patients who received BXD showed improvements with an effect size of 0.3–0.88. In the current study, the sample size was estimated with an average effect size of 0.6. The sample size required to achieve a statistical difference was estimated to be 22 patients per group (at *α* = 0.05, power = 80%, with a 95% confidence interval). Taking the dropout rate of 15% into consideration, a sample size of 84 patients (42 patients per group) is preferred. An interim analysis will be conducted to determine the adequacy of the sample size.

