### Randomization

In the present study, 84 patients with *Wei-Pi* syndrome will be randomized into the BXD or waitlist control group in a 1:1 ratio, after obtaining informed consent. The block randomization method will be employed; random codes will be generated by means of the SPSS software and placed in opaque envelopes. The principal investigator will be responsible for the maintenance of the opaque envelopes.

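### The planning effect of 0.6 comes from improvement in BXD patients, apparently without a comparator, and 22 per group does not fit the two-group test, so the stated 80% power does not hold for BXD versus waitlist

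*Protocol article*

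**What the plan says.** In the protocol article, under Sample size, the only source given for the planning effect is the investigators' pilot work, in which "the global score of FDDQL pertaining to the patients who received BXD showed improvements with an effect size of 0.3–0.88". The section continues: "the sample size was estimated with an average effect size of 0.6". It then states: "The sample size required to achieve a statistical difference was estimated to be 22 patients per group", with alpha and power given as "0.05, power = 80%, with a 95% confidence interval". The final number follows: "Taking the dropout rate of 15% into consideration, a sample size of 84 patients (42 patients per group) is preferred". An interim analysis is to check whether the sample size is adequate.

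The trial built on these figures is a two-arm comparison. Under Randomization, patients are "randomized into the BXD or waitlist control group in a 1:1 ratio". Under Primary outcome, "the primary outcome will be the variation in the scores pertaining to the global scale of the Quality of Life Questionnaire". That instrument, the FDDQL, is assessed after 3 weeks. Under Statistical analysis, continuous data are compared by t test or Wilcoxon rank-sum test. Waitlist patients are observed for 3 weeks before treatment, and under Concomitant treatment, "Medications and standard care for postprandial distress syndrome will not be restricted".

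**The concern.** The pilot sentence describes change in treated patients only. The trial will estimate something else: the change on BXD minus the change on waitlist. The two coincide only if waitlist patients do not change on average and if the effect is expressed in the SD that the two-group test uses. The section says nothing on either condition. Patients enter with symptoms, keep their usual medication and are contacted weekly, so some improvement without BXD is plausible.

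The sample size raises a second doubt. For a two-group comparison at 0.6 SD, 22 per group is about half of what is usually needed, which suggests that before-after thinking may have reached the formula as well as the effect.

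At stake is how the result will be read. If the trial finds no significant difference, readers will set that against a claimed 80% power. If the real power for the between-group test is lower, a moderate benefit could be missed and the result taken as evidence against it.

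**Working it through.** **Inputs from the article:** pilot effects 0.3 to 0.88; planning effect 0.6; alpha 0.05; power 80%; 22 per group before dropout; 15% dropout; 42 per group. Sidedness is not stated; the reference to a 95% confidence interval points to a two-sided test, which I assume.

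**Planning effect.** (0.3 + 0.88)/2 = 0.59, rounded to 0.6.

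**Reproducing 22 per group.** With z values 1.960 and 0.842, (1.960 + 0.842)² = 7.85.

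- One-sample or paired: n = 7.85/0.6² = 21.8, so 22 (24 with the t distribution).
- Two-sample, two-sided: n = 2 × 7.85/0.6² = 43.6, so 44 per group (45 with the t distribution).
- Two-sample, one-sided: 35 per group (36 with the t distribution).

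At the stated 0.6, then, 22 is the paired result, or half of 44 if a per-group number was read as a total. A two-sample t calculation at 0.88, the top of the pilot range, gives 21.3 and also rounds up to 22, but the article says that 0.6 was used.

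**Dropout.** 22/0.85 = 25.9, so 26 per group, not 42. The figure 42 does equal 35/0.85 = 41.2 rounded up, the one-sided two-sample size, but the article does not state that route.

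**Power of the planned comparison.** Two-sided two-sample t test, alpha 0.05. Of 42 per group, 42 × 0.85 = 35.7, about 36, remain after dropout. As a check by normal approximation at 36 per group: 0.6 × √(36/2) − 1.960 = 0.586, giving 72%; the t-based value is 71%. The last three rows subtract an assumed waitlist improvement from 0.6, in the same SD units; the article gives no figure for it.

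| Assumed waitlist change (SD) | Net difference (SD) | 22 per group | 36 per group | 42 per group |
|---|---|---|---|---|
| 0 | 0.6 | 49% | 71% | 78% |
| 0.1 | 0.5 | 37% | 55% | 62% |
| 0.2 | 0.4 | 25% | 39% | 44% |
| 0.3 | 0.3 | 16% | 24% | 27% |

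The last row also applies to the pilot's own lower value of 0.3 with no waitlist change. At the upper value of 0.88, power with 36 per group is 96%.

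**Smallest difference detectable with 80% power:** 0.62 SD with 42 per group and 0.67 SD with 36.

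**Units of 0.6.** If it is in baseline-SD units, its value in change-SD units is 0.6/√(2(1 − r)), where r is the correlation between baseline and week 3. For an assumed r of 0.3, 0.5 and 0.7 this gives 0.51, 0.60 and 0.77.

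**The case against.** A reader might infer that the pilot effect is certainly before-after, that it was entered as a between-group difference, and that the true effect is therefore overstated. The article does not support this much.

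- It never calls the pilot uncontrolled and never defines the effect size. Silence about a comparator in a condensed article is not proof that there was none.
- Entering 0.6 into a two-sample formula would have given 44 or 45, not 22, so that route is not shown.
- Overstatement requires average improvement on the waitlist, which the article does not quantify. FDDQL is not an entry criterion and symptoms must have begun at least 6 months earlier; both weaken the argument from regression to the mean. Unrestricted medication and telephone contact apply to both arms. The Control group section mentions a nocebo effect, and deterioration on the waitlist would widen the difference.
- The unit conversion can move 0.6 either way.

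All of this stands, and it limits what can be said about the size of the effect. It is also fair that the first fall below 80% comes from the sample-size formula and dropout, since power with 36 per group is 71% with no waitlist change at all. If the test were one-sided, 42 per group would roughly suffice at 0.6, though 22 would remain unexplained.

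The planned interim check of the sample size bears on this uncertainty, but the article states no target for it, and an effect that is not defined between groups is a poor benchmark. None of these points makes 22 per group right for a two-sided two-group test at 0.6, or supplies the missing comparator, SD or waitlist change.

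**Conclusion.** The point holds in a limited form. The planning effect describes improvement in treated patients, apparently without a control, and it sizes a between-group comparison with no allowance for waitlist change. The stated 22 per group with 80% power is not correct for that comparison, assuming a two-sided test.

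The trial plans 42 per group, so its own shortfall at 0.6 SD is small before dropout (78%) and moderate after it (71%, if those lost contribute no information). The 49% belongs to the stated 22, not to the number to be enrolled. The larger losses, 55% down to 24% with 36 per group, depend wholly on an assumed waitlist improvement of 0.1 to 0.3 SD in the same units as 0.6. That the effect is overstated is likely but not shown.

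**What to change.** Rewrite the Sample size paragraph:

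1. State whether 0.3 to 0.88 is a within-patient change, whether the pilot had a comparator, and which SD standardises the effect.
2. Restate the planning target as a between-group difference in FDDQL change at 3 weeks, with its SD and the assumed waitlist change written out.
3. Replace the statement of 22 per group and 80% power with two-sample power at 36 to 42 per group for net differences of 0.3 to 0.6 SD, and state the sidedness of the test.
4. Give the smallest difference detectable with 80% power: about 0.62 SD with 42 per group and 0.67 SD with 36.
5. Quote a baseline-adjusted figure only if ANCOVA is adopted, which the article does not plan, and label it as conditional: 0.67 × √(1 − 0.5²) = 0.58 SD with 36 per group if r = 0.5.

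The cost is one rewritten paragraph and a less favourable stated power. No extra patients are needed. The rewrite does not raise the power; it lets a null result be read against the power that the trial has.

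### The 22 patients per group do not follow from the stated inputs for a two-group comparison, the 84 do not follow from the 22, and 84 give less than the stated 80% power if the test is two-sided

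*Protocol article*

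**What the plan says.** All the figures stand in one short paragraph of the protocol article, Statistical methods, Sample size.

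- **Effect size.** Pilot data are summarised as "the patients who received BXD showed improvements with an effect size of 0.3–0.88", and then "the sample size was estimated with an average effect size of 0.6". No pilot control group is mentioned.
- **Error rates.** Alpha is 0.05 and power is 80%, followed by "with a 95% confidence interval". Sidedness and the formula are not given.
- **Size before dropout.** "The sample size required to achieve a statistical difference was estimated to be 22 patients per group".
- **Size after dropout.** "Taking the dropout rate of 15% into consideration, a sample size of 84 patients (42 patients per group) is preferred".
- **Interim look.** The same paragraph says that an interim analysis will judge whether the sample size is adequate.

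The design that these numbers serve is a comparison of two parallel groups. Under Randomization, patients "will be randomized into the BXD or waitlist control group in a 1:1 ratio". Under Statistical analysis, "Continuous data will be analyzed by means of the *t* test or Wilcoxon rank-sum test". The primary outcome is the change in the FDDQL global score at 3 weeks, and the Discussion describes the comparison as one against the waitlist group.

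**The concern.** For two independent groups, an effect of 0.6 SD at the usual error rates needs somewhat more than 40 patients per group. A requirement of 22 is about half of that. Separately, a 15% dropout allowance raises a sample size by a factor of 1/0.85, or about 1.18, whereas going from 22 to 42 nearly doubles it. So two links in one chain look broken: from the inputs to 22, and from 22 to 42.

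Two things are at stake. The article claims 80% power for its primary comparison, and readers will weigh a null result against that claim. And a paragraph that names 22 per group as the requirement also announces an interim check of adequacy. If that check took 22 as its yardstick, it would be measuring against a size with roughly even odds of detecting the planned effect.

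**Working it through.** **Inputs, all from the Sample size section unless noted:** d = 0.6; alpha = 0.05; power = 80%; dropout = 15%; two groups 1:1 (Randomization); t test or rank-sum test (Statistical analysis). Sidedness is not stated. Two-sided is taken as the main reading, because alpha 0.05 is paired with a 95% confidence interval; one-sided is shown as a variant.

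**1. Where 22 can come from.** With z(0.975) = 1.960 and z(0.80) = 0.842, the squared sum is 7.849.

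- One-sample (before-after), normal approximation: n = 7.849 / 0.6² = 7.849 / 0.36 = 21.8, so **22**. The exact one-sample t test gives 24.
- Two-sample, two-sided t test at d = 0.88, the top of the pilot range: also 22. The article, however, says that 0.6 was used.

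**2. What two groups need at d = 0.6.**

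- Two-sided: n per group = 2 × 7.849 / 0.36 = 43.6, so 44 (normal); **45** by noncentral t.
- One-sided 5%: (1.645 + 0.842)² = 6.183, and 2 × 6.183 / 0.36 = 34.3, so **35** (normal); 36 by t (power at 35 is 79.96%).

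Neither gives 22.

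**3. The dropout step.**

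- 22 / 0.85 = 25.9, so 26 per group, 52 in total.
- To need 42 randomised for 22 completers, dropout would have to be 1 − 22/42 = 48%.
- In reverse, 42 × 0.85 = 35.7, so 35 to 36 evaluable per group.

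The mismatch between 22, 15% and 42 does not depend on the test or on its sidedness.

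**4. Power at d = 0.6, alpha 0.05** (noncentral t with 2n − 2 degrees of freedom and noncentrality 0.6 × √(n/2)).

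| Evaluable per group | Two-sided t | Two-sided normal | One-sided t |
|---|---|---|---|
| 22 | 49.4% | 51.2% | 62.3% |
| 35 | 69.7% | 70.9% | 80.0% |
| 36 | 70.9% | 72.1% | 80.9% |
| 42 (no dropout) | 77.6% | 78.5% | 86.0% |
| 45 | 80.4% | 81.2% | 88.1% |

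**5. Effect detectable with 80% power, two-sided t:** 0.86 SD at 22 per group, 0.67 SD at 36 and 0.62 SD at 42.

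**6. Size for 80% power, two-sided, after 15% dropout:** 44/0.85 = 51.8 and 45/0.85 = 52.9, so 52 to 53 per group, 104 to 106 in total.

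**7. If a baseline-adjusted analysis were adopted** (none is named in the article). With 0.6 taken in outcome-SD units, the effective effect is 0.6/√(1 − r²). At 36 per group, two-sided:

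- r = 0.3: 0.6/√0.91 = 0.629, power about 75%.
- r = 0.5: 0.6/√0.75 = 0.693, power about 83%.

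The correlation r is an assumption; the article gives none.

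**The case against.** The strongest reply concerns the 84. Sidedness is not stated. A one-sided 5% test needs 35 per group by the normal approximation, and 35/0.85 = 41.2 rounds up to exactly 42. On that reading the number to be randomised has a coherent two-group derivation at the stated effect, alpha, power and dropout, and only the intermediate 22 is wrong. This stands as a possibility. It is not the better reading, because the article mentions no one-sided test and pairs alpha 0.05 with a 95% confidence interval. It also leaves the paragraph in need of correction: 22 per group gives only 62% power one-sided, and the text arrives at 42 from 22, not from 35.

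Second, a reader might infer that the investigators certainly used a before-after formula. The match at 21.8, and an effect size described only in treated patients, make that likely. But no formula is named, the exact one-sample t test gives 24, and a two-sample t test at 0.88 also gives 22. The origin remains an inference, and the point does not need it.

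Third, a reader might infer that the trial will run at about even odds, or that heavy losses would be tolerated because 22 are thought enough. The documents do not support this. The plan is to randomise 84, not 44, and nothing says that 22 completers would be accepted. The 49% describes the stated requirement, not the planned trial.

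Fourth, the shortfall at 42 per group is small if nobody drops out: 77.6% by t and 78.5% by the normal approximation. That is fair. The clear gap appears only once the plan's own 15% is applied.

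**Conclusion.** The point holds. As written, 22 per group is not the size for a two-group comparison at d = 0.6, alpha 0.05 and 80% power, under either sidedness, and 42 per group is not 22 adjusted for 15% dropout. These two statements need no assumption beyond the article's own inputs.

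The claim about the planned 84 is conditional. With a two-sided t test, power for 0.6 SD is below the stated 80% by about 2 points with no dropout and by 9 to 10 points with 35 to 36 evaluable per group. With an unstated one-sided 5% test, it would be about 80%. These figures take 0.6 as the between-group difference in SD units, an unadjusted t test, and no recovery by multiple imputation of the information lost to dropout. Under normality, the rank-sum alternative would need slightly more patients: 45/0.955, or about 47 evaluable per group two-sided.

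This should be corrected, because it is the stated basis for the trial's size and for the interim check, and correcting it is cheap.

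**What to change.** In the Sample size section:

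1. Delete the 22 per group.
2. State whether the primary test is one-sided or two-sided.
3. Restate the power for the planned 84. For a two-sided test, for example: *84 randomised (42 per group), about 36 evaluable per group after 15% dropout, gives 71% power for a between-group difference of 0.6 SD, or 80% power for 0.67 SD (two-sided t test, alpha 0.05).* If a one-sided 5% test was intended, say so and show the step from 35 to 42.
4. Say that the interim check of sample-size adequacy does not use 22 per group as its benchmark.
5. If a baseline-adjusted primary analysis is adopted, quote its power over a range of assumed correlations (about 75% at r = 0.3 and 83% at r = 0.5, with 36 per group), not at a single value.

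The cost is one rewritten paragraph and, on the two-sided reading, a less favourable stated power. No extra patients are required. Holding 80% power for 0.6 SD with a two-sided unadjusted test would instead take 104 to 106 patients in total; that is a choice for the investigators, not a consequence of the correction.
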